### Outcomes

The principle evaluation criterion is the epidemiological efficacy read out: dengue infection sero-conversion. Sero-conversion to dengue virus exposure will be measured by an enzyme-linked immunosorbent assay (ELISA) for immunoglobulin (Ig)G titres using repeated saliva samples taken sequentially during three cross-sectional studies at months 0, 3 (end of month 2), and 5 (end of month 4) during the intervention (In2Care® trap placement) period each year in both treatment and control sites. These time points are designated Pre-, Post1, and Post2 within each year.

The secondary evaluation criterion is the entomological read out. To measure the impact of the In2Care® traps on the adult mosquito population densities, 20 GATs will be placed in each of 10 randomly selected treatment and 10 control sites matched with intervention sites for historical dengue incidence. *Aedes* spp. (both *Ae. aegypti* and *Ae. albopictus*) adults will be counted and identified in the GATs once each week beginning 2 weeks before intervention, throughout the intervention period, and 2 weeks post-intervention. Traps will be placed both inside and outside 10 randomly selected houses within each site. Traps placed outside will be positioned against the wall of the house in an area with shelter from direct sunlight. Traps placed inside the house will be positioned in a suitably unobstructed area but where there is air movement.

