In2Care® traps will be placed in open areas outside of the house. GATs will be placed inside and outside houses at designated locations. GATs will be assembled as per the manufacturer’s instructions and filled with water to which a handful of dry grass/hay will be added. A sticky strip is placed inside the GAT and used to capture entering mosquitoes (Additional file 3). The general state of the traps (In2Care® and GATs) will be assessed during the weekly GAT counts and water replenished where necessary. Likewise, the dried grass and water in the GATs will be replaced during the weekly survey. After 6 weeks, the netting, active ingredient, and yeast tablets from the sachet of the In2Care® mosquito trap will be replaced with a new sachet and new water. At the end of the 4-month treatment period, all mosquito traps will be removed, properly cleaned, and stored until the following year.

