#### Adult mosquito spatial distributions (relative densities) using GATs

Weekly adult mosquito catches will be analysed by fitting a GLMM with the response variable as mosquitoes/trap/week, time (week), and intervention (Y/N) as fixed effects, and cluster ID and cluster risk designation as random effects. In addition, we will include occurrence of any public health mosquito control intervention performed in the cluster by counting the numbers of days during the 2 month inter-saliva sampling period when mosquito numbers could have been affected by such a control intervention (up to 14 days maximum post-control) as a random factor. We will test for over-dispersion in the response variable and, if it exists, an over-dispersion parameter will be estimated and applied. Otherwise, a Poisson distribution will be assumed. Two models will be constructed, one for each *Aedes* dengue vector species.

Additionally, a second series of analyses involving the distance of GATs from the nearest In2Care® trap will be analysed using log-linear regression, fitting the actual Euclidean distance in metres as a continuous variable. Because the extent to which an area is built up can impede mosquito flight (i.e. barriers), each cluster will be categorised into an urban typology (categorical building density) and this will be fitted as a factor in the analyses.

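### GATs stand inside and outside the same houses and In2Care traps only outdoors, but neither mosquito analysis includes GAT position or house, so the planned effect cannot show where adult density fell

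*Protocol article*

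**What the plan says.** The Outcomes section of the protocol article gives the purpose of the GATs: "To measure the impact of the In2Care® traps on the adult mosquito population densities". It specifies that "20 GATs will be placed in each of 10 randomly selected treatment and 10 control sites", and then: "Traps will be placed both inside and outside 10 randomly selected houses within each site". It sets different siting conditions for the two positions: a sheltered spot against the outer wall, or an unobstructed indoor spot with air movement.

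The Intervention section repeats that "GATs will be placed inside and outside houses at designated locations". Of the device under test it says: "In2Care® traps will be placed in open areas outside of the house".

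The section on adult mosquito distributions under Statistical analyses lists the terms of two analyses.

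- **Weekly catch model.** It has the "response variable as mosquitoes/trap/week, time (week), and intervention (Y/N) as fixed effects, and cluster ID and cluster risk designation as random effects", plus a random factor for days affected by public health control. It is fitted once per *Aedes* species.
- **Distance regression.** It relates catch to the nearest In2Care trap, "fitting the actual Euclidean distance in metres as a continuous variable", with a building-density category assigned to each cluster.

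GAT position and house appear in neither list, and no analysis by position is described elsewhere.

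**The concern.** Position is a deliberate, balanced factor of the GAT design. The intervention sits on one side of it, and the stated model ignores it. The weekly model therefore returns one intervention coefficient per species, averaged over inside and outside traps and weighted by where the catch is larger. A reader will want to know whether density fell inside houses as well as around the outdoor devices. The single coefficient cannot answer that, although the paired layout could.

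Two smaller matters follow. A fall confined to one position is diluted in the pooled figure and may go undetected if that position contributes little of the catch. In the distance regression, the unmodelled inside/outside difference goes into the residual.

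This is not detail left to an analysis plan. The article fixes the model terms, the over-dispersion rule and the number of models. It even adds a factor for building density because built-up areas impede mosquito flight.

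**Working it through.** **Inputs from the protocol article.** 20 GATs per monitored site, 10 houses per site, 10 sites per arm (Outcomes).

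**Layout check.** 20 / 10 = 2 GATs per house, and 10 × 20 = 200 GATs per arm. One inside and one outside per house is the natural reading, but the text does not say so house by house.

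**Inputs assumed, because the documents give none.** Outdoor share of the baseline catch, s: 20% to 80%. Size of an outdoor-only fall, f: 30% to 70%. Indoor change: none.

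**Step 1: what the planned coefficient returns.** With equal trap numbers per position in both arms, the pooled rate ratio is (1 − s) + s(1 − f) = 1 − s·f, so the reported fall is s·f.

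| Outdoor share s | f = 30% | f = 50% | f = 70% |
|---|---|---|---|
| 20% | 6% | 10% | 14% |
| 50% | 15% | 25% | 35% |
| 80% | 24% | 40% | 56% |

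The indoor fall is zero in every cell. The same figure has several explanations. An overall fall of 25% fits 25% at both positions. At s = 50% it also fits 50% outdoors only (0.5 × 0.5) or 50% indoors only.

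**Step 2: which added term helps.** Poisson log-link models fitted to expected counts with f = 50% gave:

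| Outdoor share s | Planned model | Position as main effect only | With intervention-by-position |
|---|---|---|---|
| 20% | 0.90 | 0.90 | inside 1.00, outside 0.50 |
| 50% | 0.75 | 0.75 | inside 1.00, outside 0.50 |
| 80% | 0.60 | 0.60 | inside 1.00, outside 0.50 |

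A position main effect alone leaves the intervention rate ratio unchanged. Only the interaction, or position-specific estimates, shows where the effect lies.

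**Step 3: could the effect be missed?** This was simulated with 10 v 10 clusters, 10 houses and 17 weeks. Assumed log-scale SDs were 0.4 between clusters, 0.4 between houses and 0.3 between traps. Cluster totals were compared by t test. For a 50% outdoor-only fall, the pooled effect was significant in about 71%, 53%, 29%, 15% and 8% of trials at outside:inside ratios of 4:1, 2:1, 1:1, 1:2 and 1:4. Because the fall in total catch is real, these figures are power, not false-positive rates.

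**Step 4: distance regression.** For an inside/outside ratio r in either direction, half the traps at each position adds (ln r)²/4 to the residual log variance. If v is the other trap-level log variance, the reported standard error of the slope is multiplied by √[(v + 0.25(ln r)²)/v]. With v assumed to be 0.25 or 0.5:

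- r = 2: √(0.370/0.25) = 1.22 and √(0.620/0.5) = 1.11
- r = 3: √(0.552/0.25) = 1.49 and √(0.802/0.5) = 1.27

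Both GATs at a house lie at nearly the same distance from the nearest In2Care trap. Position is therefore almost unrelated to distance, and the slope is not biased. For the same reason, the distance analysis cannot stand in for an analysis by position.

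**The case against.** The strongest reply is that nothing in the stated target is biased. The outcome is adult density overall, positions are the same in both arms by design, and the pooled effect is a proper average. If outdoor catch halves and indoor catch holds, total catch really has fallen. That stands. A reader might infer that the plan would produce a false positive, or that an outdoor-only fall would always be presented as a general one. The documents support neither. A significant pooled effect would reflect a real fall, and with a mainly indoor catch the likelier result is a missed effect.

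Two further inferences are tempting and also fail.

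- **Uneven loss of indoor GATs between arms creating a spurious fall.** The Study limitations section says only that acceptance of the devices may be a problem. It says nothing about indoor GATs or a difference between arms.
- **The position contrast detecting an outdoor-only fall almost every time.** That holds only if the outside:inside ratio is constant across clusters. With an assumed between-cluster SD of 0.4 to 0.6 on the log ratio, power is about 94% to 67% for a 50% outdoor fall and about 43% to 23% for a 30% fall.

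It is also fair to say that the remarks on built-up areas concern movement across neighbourhoods, not house walls. The mechanism described acts on larval habitats and on contaminated females, so it may lower density everywhere. The documents give no reason to expect a 50% fall outdoors and none indoors; that case is an illustration.

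What remains is that the model is stated, a balanced design factor is left out of it, and the resulting coefficient cannot locate the effect.

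**Conclusion.** The point holds as a gap in what the mosquito analyses can show, not as a bias. The overall intervention effect is valid with positions balanced, but it cannot separate indoor from outdoor change. A 50% outdoor-only fall would be reported as 10% to 40% over assumed outdoor catch shares of 20% to 80%. The cost in the distance regression is one of precision. Omitting position inflates the reported standard error of the slope by 11% to 49% under the variances and the 2:1 to 3:1 ratios assumed here. Modelling house may offset part of that gain, because two traps at one house are not independent readings of distance.

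The catch shares, fall sizes and variances are all assumptions. The layout, the outdoor-only In2Care traps and the missing terms are in the text. The point concerns the entomological read-out, which the Outcomes section makes secondary; the sero-conversion analysis is unaffected. It is worth changing because the improvement is nearly free.

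**What to change.** In the section on adult mosquito distributions:

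- Add GAT position (inside/outside) as a fixed effect and house as a random term to the weekly model for each species and to the distance regression.
- Add an intervention-by-position term to the weekly model.
- Report the intervention effect for inside and for outside GATs as a pre-specified secondary breakdown, beside the overall effect.

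The cost is a few model terms and two more reported estimates per species, with no extra traps or visits. The weekly count record must carry position and house for each GAT; the article does not say whether it does. The position-specific estimates will be less precise than the pooled one. The interaction may have limited power if the inside:outside ratio varies between clusters, so a non-significant interaction should not be read as evidence of equal effects. The change should be made before catch data are seen, since a later split would be post hoc.

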### Study subject eligibility criteria

Inclusion criteria include: male and female individuals 6–16 years old; a parent/guardian giving informed consent for the child’s participation in the study; and, for children > 7 years old, required assent for his/her participation in the study and written assent from children 12–16 years old.

The exclusion criterion is a child with known concomitant pathology(ies) at the time of the consent as indicated by the parent/guardian

### Recruitment

In each *barangay* pre-selected to participate in the study, Research Institute for Tropical Medicine (RITM) team members will hold general information meetings on the project with the population in the presence of the community (*barangay*) health workers (BHWs) and local public health officials. Because the volunteers to be recruited are of school age, additional information meetings will be held in the local schools. Once clusters are identified and randomly assigned with appropriate stratification, the study team will perform household visits with the Lipa City public health staff and respective area BHWs. The visit will explain the study and study protocol in detail and request individual informed consent/assent for periodic saliva sampling and mosquito trap placement by each household head (In2Care® and/or GATs) in and around participant’s houses (See Ethics approval and consent to participate below).

Following signed consent, a short questionnaire pertaining to the participant will be completed and the individual assigned a unique identifier barcode. The questionnaire will be completed on paper including details on: name, address, age, sex, whether having received the Dengvaxia® vaccine (and if yes, how many injections) or not, and the attending school and year (grade). The individual’s barcode will be placed next to their name on the consent form and kept in a separate file. Subsequent samples will also be labelled with a unique barcode and linked back to the individual’s barcode in the questionnaire.

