### Study type

The study is a parallel, two-armed cluster randomised trial (PCRT) evaluating the efficacy of the In2Care® mosquito trap for reducing incidence of dengue infection over a 2-year period using 4 consecutive months of treatment each year.

Previous studies have estimated that, to account for the unpredictable spatio-temporal heterogeneity in dengue transmission, PCRTs are the most effective study design and that a larger number of clusters with fewer children per cluster provide the optimal strategy—in effect, a bet-hedging approach for a statistically sufficient coverage of an area [31]. In order to attempt to control for the spatial heterogeneity in dengue occurrence, 46 areas (hereafter referred to as “clusters”), each of approximately 200 m in radius, will be pre-selected. Twenty-three clusters will be assigned to the treatment arm with In2Care® traps and 23 to the control arm without traps. Cluster sites assigned to treatment versus control arms will be matched according to retrospective incidence of reported dengue clinical cases over the previous 5 years and human population density (See Stratification scheme below). Because of ‘edge effects’, where individuals near the periphery of the treatment area will be potentially subject to contact with mosquitoes coming from neighbouring non-treated areas, we will implement the “fried egg” design [32] whereby we will assess sero-conversion only in children resident at least 50 m from the treatment zone edge. Thus, whilst we will implement In2Care® traps throughout a 200 m radius circle, we will only consider sero-conversion in children within a 150 m radius (Fig. 1). One hundred schoolchildren (between 6 and 16 years of age) will be recruited for repeated sero-conversion observation within the inner circle of each of the 46 clusters (See Sample size calculations below). As the population density in clusters will vary, it is possible that there will not be sufficient children within a prescribed area. In this case, we will increase the circle radius to reach the required sample number.

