**Fig. 3 Fig3:**
[figure not shown]
Time schedule of enrolment, interventions, and post-allocation data collections (based on SPIRIT 2013 figure [37]). HH Household

For the intervention study, 46 clusters will be selected each covering an area with at least 100 children. Mean child (age 6–16 years) densities in urban sites are 18/ha (/0.01 km^2^). Thus, an average sampling radius of 140 m (6.15 ha) would generate 100 children (excluding 10% outright refusal) to be recruited with an additional 50 m radius buffer zone for treatment but without saliva sampling. The area to be treated would thus be 113,000 m^2^ per cluster and would require 113 AD devices at a density of 1 trap/1000 m^2^ per treated cluster (23 study clusters to be treated). Before geolocalisation of historical dengue cases, however, we cannot predict which sites will be selected, nor their actual human densities, and thus the initial calculations are based on mean densities.

Treatment of areas with In2Care® devices will be carried out for 4 months each year and the active ingredient sachet (combination PPF + fungus) replaced every 6 weeks. Each In2Care® trap will be assembled (Additional file 2) and filled with 3.5–4.5 l of clean tap water. One pesticide-treated netting removed from the active ingredient sachet will then be placed on the floater and the remaining contents of the sachet tipped into the water. Each (10 × 18 cm) sealed aluminium refill sachet contains: 0.5 g In2Mix (containing 10% *Beauveria bassiana* strain GHA (Chemical Abstracts Service (CAS) No. 63428–82-0), 74.03% pyriproxyfen (CAS No. 95737–68-1), 0.97% pyriproxyfen impurity, and 15% insert silicon dioxide); one 5 × 49 cm gauze strip; and two yeast food supplement tablets of common brewer’s yeast (*Saccharomyces cerevisiae*). The tablets are added to the trap tap water to emit organic odours attractive for egg-laying mosquitoes.

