### Saliva sampling and biological analyses

A saliva sample will be taken by spitting into a sterile urine collection container, kept on ice, and transported to RITM for further processing. A 1-mL aliquot will be placed in a labelled Eppendorf® tube for storage at −20 °C. Sampling will occur just prior to, during (after 2 months of trap deployment), and at the end of the 4-month intervention period for 2 successive years. Sero-conversion testing will be performed using an in-house ELISA developed by Institut Pasteur [38] in duplicate on “paired” pre-/concurrent/post-samples from the same individual for each season. Although IgM titres will rise during a secondary DENV infection, a significant increase in IgM titres only systematically occurs in primary dengue infections and is relatively short lived; therefore, changes in IgG titres will be measured [38]. Exposure to dengue virus will produce an increase in IgG titre compared with the baseline titre in an individual, irrespective of whether they have been vaccinated or not or having been previously exposed to any DENV serotype (See Statistical analyses below). The technicians performing the ELISAs will have no prior knowledge whether the samples come from a treatment or control site. Upon study completion, analyses, and publication, all saliva samples will be destroyed and coding files erased.

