## Study limitations

The major concern of the study will be the dependency on there being sufficient dengue activity during at least one of the study years and that the cluster design is sufficient to account for the recognised spatio-temporal heterogeneity in dengue [58, 59]. To maximise power and somewhat alleviate this concern, sero-conversion rather than dengue case incidence will be used as the measure of epidemiological outcome, capturing the sub-clinical infections that form the majority of dengue infections [60, 61]. Continued compliance of participants during the 2 years may pose a problem as will community acceptance of the In2Care® traps and GAT devices. Considerable effort will be given to continuous dialogue with the community to maintain adherence throughout the study.

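### Children are enrolled after cluster allocation through a consent request that differs by arm, so the cohorts can differ by selection, to an extent and in a direction the protocol does not fix

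*Protocol article*

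**What the plan says.** All references are to the protocol article.

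- **Order of events (Recruitment).** "Once clusters are identified and randomly assigned with appropriate stratification, the study team will perform household visits". Individual consent is sought at these visits, so enrolment follows allocation.
- **Content of the request (Recruitment).** The visit is to "request individual informed consent/assent for periodic saliva sampling and mosquito trap placement by each household head (In2Care® and/or GATs") in and around the homes of participants.
- **Difference between arms (Study type).** "Twenty-three clusters will be assigned to the treatment arm with In2Care® traps and 23 to the control arm without traps". No dummy trap is described for control clusters. Under Outcomes, GATs go to 10 houses in each of 10 sites per arm, so 13 of the 23 clusters in each arm have none.
- **Masking (Saliva sampling and biological analyses).** "The technicians performing the ELISAs will have no prior knowledge whether the samples come from a treatment or control site". No masking of recruiters, health workers or families is described.
- **Refusal and shortfall.** The Intervention section plans on a radius that "would generate 100 children (excluding 10% outright refusal) to be recruited", one refusal figure for both arms. Study type says of clusters with too few children: "In this case, we will increase the circle radius to reach the required sample number".
- **Acceptance (Study limitations).** The protocol itself expects that "community acceptance of the In2Care® traps and GAT devices" may be a problem.
- **Adjustment (Sero-conversion).** The model includes age, sex, vaccination status and site baseline seroprevalence.

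**The concern.** Randomising clusters balances the clusters. It does not balance which families within them agree to take part once the arm is known. In a treated cluster the family hears a request that includes an insecticide device near the home; in most control clusters it hears a request for saliva only. If agreement depends on that difference, and those who decline differ in dengue risk, the two cohorts differ before any trap has acted.

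The plan would also tend to hide this. A treated cluster that loses families to refusal can still reach 100 children by drawing from a slightly larger circle, so equal cluster sizes would be no evidence of equal selection.

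The primary sero-conversion comparison is at stake. The recruitment questionnaire records age, sex, vaccination and schooling, but nothing on mosquito avoidance, water storage or attitude to traps, so selection on these cannot be modelled directly. Nor can it be repaired once enrolment is complete.

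**Working it through.** **1. The plan's own figure.** Sample size calculations gives p0 = 0.03, p1 = 0.015, p = 0.0225, Zα = 1.96 and Z1–β = 1.2816.
n = 2 × (1.96 + 1.2816)² × 0.0225 × 0.9775 / 0.015² = 2054.3. The stated 2054 per arm reproduces and is not in dispute; it supplies the base for what follows.

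**2. How much room recruiters have.** At the mean density in the Intervention section, π × 140² m² = 6.16 ha. Then 6.16 × 18 = 110.8 children, and × 0.9 = 99.8. Nearly every consenting child is taken, so there is little scope for staff to choose. Selection would act through refusal and through enlarging the circle.

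**3. How refusal would be absorbed (assumption).** If 10% of the families who would otherwise join decline in a treated cluster, 99.8 × 0.9 = 89.8 children remain. Restoring the number needs a radius of 140 × √(1/0.9) = 147.6 m, an enlargement that would hardly be noticed.

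**4. Bias when the trap does nothing (assumption).** Let r be the extra refusal in the treated arm and R the risk of decliners relative to acceptors. The control cohort keeps both groups and the treated cohort only acceptors, so the null risk ratio is 1 / ((1 − r) + rR).

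| r | R | Risk ratio |
|---|---|---|
| 0.10 | 1.5 | 1/1.05 = 0.952 |
| 0.10 | 2 | 1/1.10 = 0.909 |
| 0.10 | 1/1.5 | 1/0.967 = 1.034 |
| 0.10 | 1/2 | 1/0.95 = 1.053 |
| 0.30 | 2 | 1/1.30 = 0.769 |

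The rows with r = 0.10 take extra refusal equal in size to the plan's total refusal. The last row needs three times that.

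**5. A second form of the assumption.** Suppose half the children have 2 or 3 times the risk of the other half, mean risk is 3%, and in one arm consent is 70% in the higher-risk half and 90% in the lower.
- Ratio 2: (0.7 × 0.04 + 0.9 × 0.02) / 1.6 = 2.875%, a shift of −4.2%.
- Ratio 3: (0.7 × 0.045 + 0.9 × 0.015) / 1.6 = 2.81%, a shift of −6.25%.

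Reversing the consent rates reverses the sign.

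**6. Effect on the test.** This uses 2054 per arm, a two-sided 5% test and control risk 3%, ignoring clustering as the plan's formula does.
- Trap without effect, treated cohort at 5% or 10% lower risk: false rejection is 5.9% or 8.9%. At 20% or 30% lower it would be 22% or 45%.
- True efficacy 50%, treated cohort at 5% or 10% higher risk: apparent efficacy is 47.5% or 45%, and power falls from 90% to 86% or 82%.

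**The case against.** The strongest reply is that the route to bias is narrower than it looks, and much of that reply stands.

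- **Trap hosting as an entry filter.** A reader might infer that treated children enter only if the household takes a trap. The text does not say so. The eligibility criteria require consent and assent to the child's participation, and the only exclusion is known concomitant pathology. Traps are laid by area, one per 1000 m², in open areas outside houses. The 6.15 ha sampling circle would hold about 62 traps (61,500/1000) against 100 children, so not every participant's home has one. The consent section to which Recruitment refers was not in the text reviewed, so whether the two consents can be given separately is unknown. What is left is arm-aware refusal, not a stated filter.
- **A large spurious benefit.** A reader might infer a false reduction of up to 23%. That needs 30% extra refusal and decliners at twice the risk, neither of which the protocol supports. Direction is open too: households troubled by mosquitoes may welcome traps.
- **Recruiters who know the arm.** No sentence says that they do. It is an inference from the order of events, the trap request and the absence of any masking outside the laboratory. It is a strong one.
- **Existing safeguards.** Clusters are matched on five-year incidence and population density, sero-conversion is measured from each child's own baseline, and the model carries site baseline seroprevalence. Long-standing differences in exposure should show there in part. These measures reduce the risk. They do not reach differences in willingness or behaviour within a site, and the baseline sample comes from children already selected.

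The stated order of events is untouched by any of this.

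**Conclusion.** The point holds as a risk built into the stated sequence. Allocation comes before consent, the request differs by arm, and the planned covariates cannot be relied on to remove the resulting selection. It does not hold as a demonstrated bias.

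Size and direction cannot be derived from the documents. With extra refusal of 10% in the treated arm and decliners at 1.5 to 2 times the risk, the null risk ratio is about 0.95 to 0.91, a false reduction of 5 to 9% against a target of 50%. If decliners are the lower-risk families, the bias runs towards no effect. On the plan's unclustered test, shifts of 5 to 10% raise false rejection from 5% to 5.9–8.9%, or lower power from 90% to 86–82%. These figures rest on the assumed refusal and risk ratios. The change should be made before recruitment, because it is cheap then and impossible afterwards.

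**What to change.** 1. In all 46 clusters, list eligible children and obtain consent and assent for saliva sampling, with identical wording, before the allocation is drawn or revealed.
2. Then reveal the allocation, early enough for the GAT counts, which Outcomes starts two weeks before intervention in sites chosen by arm. Holding allocation back until every Pre sample is taken would collide with that timetable; once the cohort is fixed by consent, Pre sampling can keep its planned time.
3. Seek trap-placement consent as a separate, later step, and state that it is not a condition of the child's participation. A single consent requiring willingness to host a trap would create an explicit filter in both arms.
4. Analyse every enrolled child in the assigned arm, whether or not the household accepts a trap.
5. Report households approached, refusals and any enlargement of the radius, by arm.

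The cost is two consent steps in place of one, and In2Care and GAT site logistics that can be settled only after enrolment. Sample size, assay and model are unchanged.
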